#### **15. Participants (Screening and Selection)**

a. How many participants are to be enrolled at UAB? **426 older cancer survivors**  
If multi-center study, total number at all centers: \_\_\_\_\_

b. Describe the characteristics of anticipated or planned participants.  
Sex: **Male and Female**

Race/Ethnicity: **Our sample will represent the state population for race-ethnicity (27% minority).**

Age: **65 and older**

Health status: **Men and women recently diagnosed with a cancer of favorable prognosis (localized and regional staged female breast, and**

prostate cancers; localized colon & rectum, uterine cervix & corpus, kidney/renal pelvis, non-Hodgkin lymphoma, oral cavity/pharynx, and esophagus cancers; and in situ bladder cancer); and have no medical conditions that would preclude gardening or the consumption of a diet high in fruits and vegetables (e.g., pharmacologic doses of warfarin) – see inclusion/exclusion criteria following page.

*Note. If data from prior studies indicate differences between the genders or among racial/ethnic groups in the proposed research or if there are no data to support or to negate such differences, Phase 3 clinical trials will be required to include sufficient and appropriate entry of gender and racial/ethnic subgroups so that trends detected in the affected subgroups can be analyzed. If ethnic, racial, and gender estimates are not included in the protocol, a clear rationale must be provided for exclusion of this information. If prior evidence indicates that the results will not show gender or racial differences, researchers are not required to use gender or race/ethnicity as selection criteria for study participants. They are, however, encouraged to include these groups. See Section II. Policy of the NIH POLICY AND GUIDELINES ON THE INCLUSION OF WOMEN AND MINORITIES AS SUBJECTS IN CLINICAL RESEARCH – Amended, October, 2001) for further details.*

c. From what population(s) will the participants be derived?

**Please note that as in previous studies, like our ENERGY trial (F100325003), we will ascertain cases from the Alabama State Cancer Registry and they will obtain approval from patients' oncology care physicians for us to contact their patients for this study using the letter of invitation provided in our packet of materials (note that in providing us permission to contact their patients, physicians of record also would provide their signature to include in this letter of invitation). In order to identify participants (for recruitment purposes) via the state cancer registry, we will obtain PHI prior to enrollment (see Waiver). We also will ascertain cases directly from the UAB cancer registry and from sites associated with the UAB cancer care network. Additionally, we will post an advertisement material in local newspapers to obtain self-referred participants (see attached), and also will contact individuals who had asked that we keep their names on a wait-list should we embark on another study (Electronic Database for Wait-Listed Patients UAB IRB Protocol Number: X101104003).**

Describe your ability to obtain access to the proposed population that will allow recruitment of the necessary number of participants:

**As mentioned, cancer registries will provide us with names and addresses of adult men and women (age 65 and older) living in Alabama, who have been diagnosed with loco-regionally staged cancers with good prognoses ( $\geq 80\%$  5-year relative survival) and who have been approved for contact by their oncology care provider. A direct mail approach is the best way to assure that survivors, regardless of county of residence, cancer diagnosis,**

age, race, and socio-economic status are all given an equal opportunity to participate. We have used this approach successfully in the past (ENERGY trial) and 91% of oncology care physicians within the area have provided approval for contacting their patients about diet and exercise studies. The mailing will include the letter of invitation (co-signed by the physician of record) and the study screener (see attached materials). For self-referred participants who respond to our advertisements, we will use the study screener to assess eligibility over the phone, and also will follow this procedure when we contact individuals who had asked that we keep their names on a wait-list should we embark on another study (Electronic Database for Wait-Listed Patients UAB IRB Protocol Number: X101104003). Since the activity monitor, stool and nail samples and questionnaires are likely to be completed prior to the in-home baseline visit, it will be necessary to conduct informed consent via telephone. Men and women who are deemed eligible will be telephoned and a phone consent time scheduled (see attached materials for the consent script). Participants will receive a mailed copy of the consent form as well as a postage paid envelope to return the consent. After the telephone consent has been completed and returned, the baseline visit will be scheduled. Roughly 10-12 days prior to the baseline visit, participants will be mailed questionnaires, a programmed accelerometer with instructions for a 7-day collection and a moistened wipe and collection bags for the stool and nail clipping samples. These materials will be collected by study staff during the baseline visit conducted in participants' homes.

Describe the inclusion/exclusion criteria:

We will include individuals who: (1) are diagnosed with a loco-regionally staged cancer associated with an 80% or greater 5-year survival rate (localized and regional staged female breast, and prostate cancers; localized colon & rectum, uterine cervix & corpus, kidney/renal pelvis, non-Hodgkin lymphoma, oral cavity/pharynx, and esophagus cancers; and in situ bladder cancer); (2) reside in the state of Alabama; (3) completed primary curative cancer treatments, i.e., surgery, chemotherapy or radiation therapy; (4) are at least 65 years of age; (5) are at higher risk of functional decline ( $\geq 2$  physical function (PF) limitations as defined by the SF36 PF subscale); (6) currently eat less than 5 servings of fruits and vegetables (F/V)/ day; (7) exercise less than 150 minutes/ week; (8) speak and write in English (some of our scales are not validated in other populations/languages); and (9) are willing to be randomized to either study arm and participate in the follow-up assessments. We will exclude individuals who: (1) are not competent due to mental health or other very serious comorbid conditions (e.g., severe orthopedic conditions or scheduled for a hip or knee replacement with 6 months, paralysis, unstable angina or who have experienced a myocardial infarction, congestive heart failure or pulmonary conditions that require hospitalization or oxygen within 6 months, stroke, degenerative neurological conditions); (2) have any medical condition substantially limiting moderate physical activity; (3) currently taking pharmacologic

doses of warfarin (does not include doses taken to maintain a port); (4) do not reside in a location that can accommodate 4 or more Earthboxes or 1-raised bed (4'x 8'), and that get at least 4 hours of sun a day; (5) do not have running water; (6) have recent experience with vegetable gardening, e.g. planted a vegetable garden within the past year; or (7) have a history of lymphedema flares, axillary node dissection of 10 or more lymph nodes per side.

- d. If participants will comprise more than one group or stratification, describe each group (e.g., treatment/intervention, placebo, controls, sham treatment) **and** provide the number of participants anticipated in each group.

**Participants will be recruited into 8 cohorts [From Cohort 1 (Start in Year 1) to Cohort 8 (Start in Year 3)] to achieve our accrual goal of 426 participants. Each cohort will be comprised of 52-54 participants. Participants will then be randomized to 1-of-2 study arms: 1) an intervention group that receives an immediate 1-year mentored vegetable gardening intervention in the first year (26-27 participants), or 2) a wait-listed group that receives a delayed 1-year mentored vegetable gardening intervention in the second year (26-27 participants). All participants will be on study for two years. Participants will be block randomized within 2 strata defined by the number of physical function limitations as assessed by the SF36-PFSS (2 vs.  $\geq 3$ ). Participants would be assigned with equal allocation either group A or group B below:**

**Group A:** Participants assigned to this group, would be paired immediately with a Master Gardener from the Cooperative Extension in their county of residence. They also would be given supplies (soil, plants, seeds, and fertilizer) to support either 4 earth boxes (which can be used to garden on balconies, patios or decks) or 1 raised bed garden. These supplies will be provided free of charge. Master Gardeners will make monthly visits to guide participants in setting-up the garden, maintaining it, and replanting it season-to-season. Every month, Master Gardeners also will contact survivors by telephone or email (based on survivor preference) to check-in on garden status and to field questions or problems.

**Group B:** Participants assigned to this group, would receive the exact same program as Group A (see above), but would receive it AFTER a waiting period of one year. During the wait period, UAB study staff will send participants quarterly holiday postcards reminding them about the study and letting them know that we are looking forward to delivering the program to them in the upcoming year. These postcards will encourage wait-listed participants to contact us if their address or health status changes. These postcards are planned for New Year's, St Patrick's Day, 4th of July and Thanksgiving.

- e. Indicate which, if any, of the special populations listed below will be involved in the protocol. Include the Special Populations Review Form (SPRF) if indicated.
- ☐ Pregnant Women: Attach [SPRF—Pregnant Women, Fetuses, Neonates/Nonviable Neonates](#)
  - ☐ Fetuses: Attach [SPRF—Pregnant Women, Fetuses, Neonates/Nonviable Neonates](#)

- ☐ Neonates/Nonviable Neonates: [SPRF—Pregnant Women, Fetuses, Neonates/Nonviable Neonates](#)
- ☐ Prisoners: Attach [SPRF—Prisoners](#)
- ☐ Minors (<18 years old): Attach [SPRF—Minors](#)
- ☒ Employees or students at institution where research conducted
- ☐ Persons who are temporarily decisionally impaired
- ☐ Persons who are permanently decisionally impaired (e.g., mentally retarded)
- ☐ Non-English Speakers

**For each box checked**, describe why the group is included **and** the additional protections provided to protect the rights and welfare of these participants who are vulnerable to coercion:

**Student and employees will not be targeted specifically for recruitment; however, if a potential participant is identified through the cancer registries and is a student or employee, their participation or non-participation will not affect either their employment or academic standing at UAB.**

- f. List any persons other than those directly involved in the study who will be at risk. If none, enter "None": **None**
- g. Describe the process (e.g., recruitment, chart review) that will be used to seek potential participants (e.g., individuals, records, specimens). Research recruitment by non-treating physicians/staff may require completion of Partial Waiver of Authorization for Recruitment/Screening. (See <http://main.uab.edu/show.asp?durki=61981>.)

**Cancer survivors (name and address obtained from the Alabama State Cancer Registry, as well as specific hospital registries associated with UAB or the UAB cancer care network) who live within a 15 mile radius of Master Gardener (MG) volunteers will be mailed a letter of invitation that explains the program, i.e., a 2-year program in which the participant may be randomized to the immediate gardening intervention or the delayed gardening intervention (wait-list control) where they would work with a MG and would be mentored and receive the supplies necessary to establish spring, summer and fall gardens or to a usual care group, as well as to participate in baseline and one- and two-year follow-up assessments. The letter (which would be co-signed by their physician of record) would make it clear that the program was free-of-charge, and that a small incentive of \$25 would be provided upon completion of each of the three assessments. The letter would also mention \$10 would be provided after completion of each questionnaires with return postage at 6- and 18-months. Letters will include a telephone number and encouragement will be given to call if survivors have questions or concerns, or if they wanted to enroll in the program immediately. A brief questionnaire that collects information on interest in participation and basic eligibility criteria (if interested) or reasons for disinterest (if not interested) would be included within the letter along with a pre-addressed postage-paid envelope for return. Based on a 21% response rate obtained from our previous study, we will mail letters out in 8**

batches, first starting with a batch of 265 and then mailing in progressively during a recruitment period of 2½ years until we ascertain our targeted accrual. By using this method we should get a representative and accurate assessment of uptake without putting ourselves into the position of offering the program to more survivors than we have the resources to accommodate.

- h. If you will use recruitment materials (e.g., advertisements, flyers, letters) to reach potential participants, attach a copy of each item. If not, identify the source (e.g., databases) from which you will recruit participants.

We will recruit participants primarily from lists provided by the Alabama State Cancer Registry (ASCR) as well as specific sites affiliated with UAB cancer care network. Additionally, we will post an advertisement material in the local newspapers to obtain self-referred participants. We also will contact individuals who had asked that we keep their names on a wait-list should we embark on another study (Electronic Database for Wait-Listed Patients UAB IRB Protocol Number: X101104003). The letter of invitation, eligibility screener and scripts, and the poster are attached.

- i. Describe the procedures for screening potential participants.

Participants will be mailed a screener with their letter of invitation. The cancer survivors will be asked to answer the questions on the screener if interested in participating in the study and will return to study staff in the postage paid envelope provided. (See attached screener for specific questions asked). For self-referred participants who respond to our advertisements or those in our wait-list database, we will use the study screener to diagnose eligibility over the phone.

## **16. Protocol Procedures, Methods, and Duration of the Study—in nontechnical language**

- a. Describe the procedures for all aspects of your study. Tell us what you are doing.

### **Assessments:**

To measure the impact of the program on the lifestyle behaviors and health of study participants, home visits will be scheduled with all participants (to assess survivor's health and health behaviors at baseline and at the time of consent, and then again 1-year and 2-year later. In addition to home visits, participants will be mailed questionnaires with return postage at 6- and 18-month after study start. Assessments will provide information on specific domains. The assessments are described below and are attached to this application:

### **Physical Function**

#### **SF36 Physical Function subscale (SF36 PFSS):**

This 10-item subscale assesses general physical function and is valid & reliable for use in healthy & chronically-ill adults.

### **Senior Fitness Test Battery:**

Measures physical function in four domains: (1) lower & upper body strength (30-sec chair stand, arm curl); (2) endurance (2-min step test); (3) flexibility (chair sit-&-reach, back scratch); and (4) agility/dynamic balance (8-ft Get Up & Go).

### **Grip Strength:**

Measures participant's functional limitations and disability using a dynamometer.

### **Usual and rapid gait speed:**

Predictive of functional health and mortality

### **Biomarkers of Physical Function and Healthful Aging**

Blood will be drawn in a 10cc EDTA treated vacutainer, a 9.7cc serum separator vacutainer, and a 2.7cc sodium citrate containing vacutainer allowed to clot & centrifuged immediately (portable centrifuges will be used in the field as in our epidemiologic studies). Plasma and serum would be drawn-off from each vacutainer and aliquotted into .5 ml cryovials. The samples also will be stored in -80 degree freezers under back up emergency power at Volker Hall G005 and Wallace Tumor Institute 399S until analyzed for plasma alpha carotene, telomerase, serum IL-6 and D-dimer.

### **Intestinal Microbiome**

We will be collecting a stool sample to determine the impact of the gardening intervention on the intestinal microbiome. Participants will be asked to use a moistened wipe after they have a bowel movement on the day before their home visit and to then insert the wipe into a plastic bag and record the time and date at which the sample was collected (both the wipe and plastic bag will be mailed to the participant before each of their home visits). The participant will store the sample in their home freezer until the time of the home visit and the sample will be stored in in -80 degree freezers under back up emergency power at Volker Hall G005 and Wallace Tumor Institute 399S until analysis of microbiome.

### **Cortisol Level**

We will be collecting toe and finger nail clippings and saliva samples to determine the impact of the gardening intervention on cortisol (a biomarker indicating stress). Participants will be asked to clip their toe and finger nails on the day or before their home visit and to then insert into a plastic bag and record the time and date at which the sample was collected (plastic bags and a nail clipper will be mailed to the participant before each of their home visits). UAB staff will clip the nails of participants who are unable to clip their own nails. Nail clipping samples will be handed to study staff at the time of the home visit. Saliva sample also will be collected at the time of home visit. All specimens will be stored in -80 degree freezers under back up emergency power at Volker

Hall G005 and Wallace Tumor Institute 399S until analysis of cortisol level.

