## **10. Use of Specimens**

Does this project involve collecting specimens from participants and storing them for future research? ☒Yes ☐No

**If Yes**, complete a-h. If no, skip to Item 11

a. How will specimens be obtained, processed, distributed, and stored?

**A trained phlebotomist will draw one and a half tablespoons of blood, if participants are breast cancer survivors, phlebotomy will be performed on the arm contra lateral to the cancer (the phlebotomist will verify the appropriate arm prior to each blood draw). A foil covered 10cc EDTA treated vacutainer of blood (two teaspoons), a 9.7cc serum separator vacutainer, and a 2.7cc sodium citrate containing vacutainer will be collected from all participants at baseline, 1- and 2-years follow-up to assess changes over time in biomarkers of successful aging, with the expectation that home gardening will improve these physiologic measures. Blood will be centrifuged within 30 minutes of the draw. Plasma and serum would be drawn-off from each vacutainer and aliquotted into .5 ml cryovials. The samples also will be stored in -80 degree freezers under back up emergency power at Volker Hall G005 and Wallace Tumor Institute 399S until analyzed for plasma alpha carotene, telomerase serum IL-6 and D-dimer. In addition, we will be collecting stool samples to determine the impact of the gardening intervention on the intestinal microbiome. Participants will be asked to use a moistened wipe after they have a bowel movement on the day before their home visit and to then insert the wipe into a plastic bag and record the time and date at which the sample was collected (both the wipe and plastic bag will be mailed to the participant before each of their home visits). The participant will store the sample in their home freezer until the time of the home visit and the sample will be stored in -80 degree freezers under back up emergency power at Volker Hall G005 and Wallace Tumor Institute 399S until analysis of microbiome. Fingernail and toenail clippings as well as saliva samples to assess cortisol levels are collected at the time of home visit and will be stored in -80 degree freezers under back up emergency power at Volker Hall G005 and Wallace Tumor Institute 399S until further analysis of cortisol level (plastic bags and a nail clipper will be mailed to the participant before each of their home visits and they will be encouraged to clip their own nails, but if they are unable, UAB staff will accomplish this during the home visit).**

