
b. How will specimens be labeled (e.g., unique identifier, medical record number, Social Security number, name, date of birth)?

**Specimens will be labeled with the study title, a unique study ID number, and the date and time of the blood draw and other samples collection, i.e. stool, saliva, nail clippings.**

- c. How will clinical data associated with the specimens be collected and stored?

**The database will not contain any personal identifying information to link to the subject. The specimens will have a unique identifying code (study ID number). Clinical information will be stored in a separate and protected database that links samples and other information to the subjects.**

- d. What participant-identifying information will be collected and linked to the specimens?

**Demographic, diagnosis, and treatment information will be collected on each participant in the study and will be stored in locked study files or in password protected databases.**

- e. What steps will be taken to maximize the confidentiality of linked identifiers? For example, procedures could include using a password-protected computer database to link identifiers, with limited personnel knowledgeable of the password, or coded identifiers released without the ability to link to clinical data (also called "stripped" or "anonymized" specimens).

**The specimens and related data spreadsheets will contain only the subject ID codes to prevent the ability to link personal identifiers. The database requires a secure password, and access is limited. Only research study staff who have received IRB approval are allowed access to the database.**

- f. Will specimens be shared with other investigators in the future? ☒Yes ☐No  
**If Yes**, what identifiers, clinical information and demographic information will be shared; or will the specimens be stripped of identifiers (i.e., anonymized)? Also **if yes**, outline your procedure for assuring IRB approval for release and use prior to release of specimens.

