| Stool Sample                 | <1 minute                               | 3 times (baseline, 1-year and 2-year follow-up) |  Res  Routine |

| Cortisol Level         |                                         |                                                 |                                                                          |
|-------------------------------|-----------------------------------------|-------------------------------------------------|--------------------------------------------------------------------------|
| Procedure                     | Length of Time Required of Participants | Frequency of Repetition                         | Research (Res) –OR- Routine Care                                         |
| Saliva                        | 2 minutes                               | 3 times (baseline, 1-year and 2-year follow-up) |  Res  Routine |
| Toe and finger nail clippings | 2 minutes                               | 3 times (baseline, 1-year and 2-year follow-up) |  Res  Routine |

| Anthropometrics |
|------------------------|
|------------------------|

| Procedure                    | Length of Time Required of Participants | Frequency of Repetition                         | Research (Res) –OR- Routine Care                                         |
|------------------------------|-----------------------------------------|-------------------------------------------------|--------------------------------------------------------------------------|
| Height                       | <1 minute                               | Once at baseline                                |  Res  Routine |
| Weight & waist circumference | 2 minutes                               | 3 times (baseline, 1-year and 2-year follow-up) |  Res  Routine |

| Comorbidity |                                         |                                                 |                                                                          |
|-------------|-----------------------------------------|-------------------------------------------------|--------------------------------------------------------------------------|

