**5). Subjects may be inconvenienced or embarrassed providing the stool sample.**

- b. Estimate the frequency, severity, and reversibility of each risk listed.

**1) The survey instruments that will be employed in this study, e.g., mainstream and standardized health related quality of life measures, as well as those used to assess diet and physical activity contain few (if any) psychologically sensitive questions.**

**2) We have worked diligently to reduce participant burden by employing valid survey scales that are brief. Times for each of the assessments, as**

well as for interacting with master gardeners will be scheduled at the patient's convenience, thus we will work around their schedule in order to deliver the intervention and assess its potential impact.

3) Prior to the blood draw, the phlebotomist will verify the side of the previous cancer. Blood will be drawn on the side contra lateral to the affected side. Butterfly needles will be used to perform phlebotomy and a trained phlebotomist will draw blood, thus reducing discomfort and bruising. Furthermore, we have worked to minimize the number of draws to 3 over the course of the 2-year study. This decision is based primarily on previous studies that indicate that blood levels of nutrients are seasonally-influenced, thus the optimal collection periods are 1-year and 2-year from baseline. This also results in fewer draws.

4) The main potential adverse effect is breach of confidentiality regarding health status information reported by a subject. To minimize this potential risk, all data will be stored without personal identifying information and all information will be stored in a password protected file that is only accessible by trained investigators and study staff. Although master gardeners will not collect any information, we will provide training regarding maintenance of confidentiality.

5.) Participants will receive the stool and nail clipping sample collection materials (special wipe and zip lock baggie) prior to their baseline visit so that they can collect these samples in the privacy of their own homes. This should minimize participant embarrassment and inconvenience.

- c. Is this a therapeutic study or intervention? ☐Yes ☒No  
**If Yes**, complete the following items:  
i. Describe the standard of care in the setting where the research will be conducted: \_\_\_\_\_  
ii. Describe any other alternative treatments or interventions: \_\_\_\_\_  

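### Salivary cortisol has no set collection hour, so time of day can add avoidable noise to each participant's change score

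*Protocol*

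**What the plan says.** Section 16.a (Cortisol Level) states the purpose: "We will be collecting toe and finger nail clippings and saliva samples to determine the impact of the gardening intervention on cortisol". Section 10.a names the same two specimen types: "Fingernail and toenail clippings as well as saliva samples to assess cortisol levels are collected at the time of home visit". Cortisol is thus measured in two ways, and saliva is one of them.

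The timing rule for saliva is "Saliva sample also will be collected at the time of home visit". The procedure table in section 16.e lists saliva at baseline, 1 year and 2 years, at 2 minutes each. It describes no repeat sampling within a visit. One sample per visit is a fair reading of this but is not stated outright.

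Section 18.b, item 2, explains that assessments and master gardener contacts are fitted to the participant: "thus we will work around their schedule in order to deliver the intervention and assess its potential impact". No section gives a clock window, a time since waking, or a rule that repeat visits fall at the same hour as baseline.

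The time of collection is kept. Section 10.b says that specimen labels carry "the date and time of the blood draw and other samples collection, i.e. stool, saliva, nail clippings".

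**The concern.** The premise is that salivary cortisol varies over the day. That is general physiology and is not stated in the protocol. If it holds, the difference between two saliva samples from one person contains a part that comes only from the difference in clock time. Because visits are booked freely, that part varies from person to person and widens the spread of the change score, so the comparison of arms on salivary cortisol loses precision.

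The protocol already controls timing in another respect. Section 18.b, item 3, justifies annual blood draws by seasonal variation in nutrient levels. Hour of day gets no similar treatment. When a sample is taken is a matter for the protocol: an analysis can model uneven hours afterwards but cannot make them even.

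**Working it through.** **No stated figure to reproduce.** The protocol gives no alpha, power, effect size or SD for cortisol. What can be checked is the sample size. Section 15.d recruits 8 cohorts of 52 to 54 "to achieve our accrual goal of 426 participants". 8 × 52 = 416 and 8 × 54 = 432, a range that contains 426. Equal allocation gives 426 / 2 = 213 per arm.

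**Reference point (assumed: two-sided alpha 0.05, 80% power, no dropout).** The detectable difference, in units of the SD of change with hour held fixed, is (1.960 + 0.842) × √(2/213) = 0.271.

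**Noise from visit hour.** Take the SD of a single saliva sample at a fixed hour as 1. Assume:
- within-person correlation ρ = 0.5
- a linear trend of b SD per hour
- visit hours uniform over W hours and independent from visit to visit.

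The variance of change is then:
- hour fixed: V0 = 2(1 − ρ) = 1
- hour free: V1 = V0 + 2b²W²/12.

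The SD is inflated by √(V1/V0), and the share of change-score variance due to hour is 1 − V0/V1. For example, with W = 8 and b = 0.15, 2 × 0.0225 × 64/12 = 0.24, so V1 = 1.24 and the inflation is √1.24 = 1.114.

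| W (hours) | b (SD/hour) | Share of change variance | SD inflation | Power at 0.271 |
|---|---|---|---|---|
| 4 | 0.05 | 0.7% | 1.003 | 79.7% |
| 4 | 0.10 | 2.6% | 1.013 | 79.0% |
| 4 | 0.15 | 5.7% | 1.030 | 77.7% |
| 8 | 0.05 | 2.6% | 1.013 | 79.0% |
| 8 | 0.10 | 9.6% | 1.052 | 75.9% |
| 8 | 0.15 | 19.4% | 1.114 | 71.1% |

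If people tend to book similar hours each time, the inflation is smaller than shown. If ρ is above 0.5, it is larger.

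**Larger shares.** If visit hour explained a share f of the change-score variance, the inflation would be 1/√(1 − f).

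| f | SD inflation | Power at 0.271 | Needed per arm for 80% |
|---|---|---|---|
| 10% | 1.054 | 75.7% | 237 |
| 20% | 1.118 | 70.7% | 267 |
| 30% | 1.195 | 65.0% | 305 |
| 50% | 1.414 | 50.8% | 426 |

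Nothing in the protocol says which share applies.

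**Arm difference in visit hour.** If hours are independent of arm and W = 8, the difference between arms in mean hour shift has expectation 0 and standard error √(2 × 64/12) × √(2/213) = 3.266 × 0.0969 = 0.32 hours. That is chance variation, and the standard error of the comparison already reflects it.

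**The case against.** The case against acting has four parts.

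**Little depends on saliva.** Cortisol is not in the trial hypothesis (section 13). Section 17 names the SF36 physical function subscale for the between-arm comparison, and its biomarker examples under the secondary endpoints omit cortisol. This stands, and it keeps the point minor.

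**Flexible booking is deliberate.** It limits burden in statewide home visits to people aged 65 and over with at least two physical function limitations. This also stands, and it is why the remedy should apply only where possible.

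**Collection time is recorded, and covariates belong to the analysis plan.** This stands in part. A reader might infer that the recorded time will go unused. That cannot be said, because the analysis plan is not at hand. The scheduling gap remains whatever that plan contains.

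**The size is assumed.** This is correct. The tables show a range and not an estimate.

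Two stronger readings are tempting. The first is that the whole cortisol objective is compromised. The protocol also measures cortisol in nails, and the time-of-day argument is made only for saliva.

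The second is bias between arms, for instance if gardeners came to book later visits. The hour of a follow-up visit is chosen after randomisation by people who know the allocation, so randomisation alone does not guarantee balance. But no section suggests that hours will differ by arm, and both arms have the same three visits. This is a possibility, not a finding.

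**Conclusion.** The point holds for salivary cortisol. Under the plan as written, one person's samples can come from different hours, and this adds noise that a booking rule could avoid. Under the moderate assumptions above, the SD of change rises by about 0.3% to 11%, and power at the reference effect falls from 80% to between 79.7% and 71.1%. A larger share of variance due to hour would cost more, and the documents cannot settle which case applies. The result rests on the premise of daily variation, the assumed slope, spread and correlation, and visit hours that are independent between visits. It shows a loss of precision, not bias. It is a cheap, minor improvement to a marker that is not named among the secondary endpoints.

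**What to change.** Add one instruction to section 16.a (Cortisol Level): book each participant's 1- and 2-year home visits in the same clock window as the baseline visit where possible. Participants need not share a common hour. If the time trend is the same at each visit, keeping the hour fixed within a person removes it from that person's change score.

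In addition, use the collection time already on the specimen label as a covariate in the salivary cortisol analysis, entered for each visit or as the shift in hour from baseline. This deals with visits that miss the window. If the analysis plan already provides for it, only the booking instruction is new.

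The cost is slightly less freedom in booking home visits. No new measurement is needed.
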